1 Original trial protocol and statistical analysis plan

2 Study title: A randomized controlled study for the effects of Olmesartan/Amlodipine  
3 administrated in Morning or At Nighttime on nocturnal blood pressure reduction in  
4 Chinese patients with mild-moderate essential hypertension.

5 Original Protocol: Version 2.0 10 January 2022

6

7 Introduction

8 Hypertension is the most common chronic non-communicable disease and the most  
9 important risk factor for cardiovascular disease worldwide. Moreover, hypertension  
10 significantly increases the risks of atherosclerotic heart disease, stroke, chronic kidney  
11 disease, and heart failure. According to the recent China Hypertension Survey, the  
12 age-adjusted prevalence of hypertension in Chinese adults aged >18 years is 23.2%,  
13 with the estimated number of affected patients exceeding 250 million; however, the  
14 blood pressure (BP) control rate is only 16.8%, which is significantly lower than that  
15 in the developed countries of Europe and the USA. In 2017 alone, 2.54 million  
16 Chinese individuals died as a result of high systolic BP (SBP), with cardiovascular  
17 disease being the immediate cause of death in 95.7% of cases. Therefore, effective  
18 control of BP is critical in the prevention and treatment of cardiovascular disease and  
19 for the reduction of its high mortality rate.

20 The Patient-Centered Cardiac Event Evaluation Million Population Project,  
21 which included 1.7 million community-dwelling residents aged 35–75 years in 31  
22 provinces and autonomous regions in mainland China, found that 81.1% of treated

hypertensive patients took a single anti-hypertensive agent but that the proportion of patients with uncontrolled BP on combination therapy was only 18.6%. This finding suggests that low utilization of combination therapy may be an important reason for the low BP control rate in hypertensive patients in China. The single-pill combination (SPC) is an oral antihypertensive regimen that includes two or more agents. Several clinical trials have demonstrated that SPC is safe and effective in protecting target organs, reducing/offsetting adverse reactions, increasing BP control synergistically, and lowering the incidence of cardiovascular disease and deaths from the disease. Therefore, SPC is recommended as the initial choice in the recently published international hypertension guideline. Olmesartan/amlodipine (OA) is a novel SPC formed by the combination of an angiotensin receptor antagonist and a calcium ion blocker and may effectively lower peripheral vascular resistance and have an antihypertensive effect without affecting glucose or lipid metabolism. Previous large-scale clinical studies have confirmed that OA can significantly reduce BP in hypertensive patients who do not meet their BP target on monotherapy. However, those studies used only office BP as the indicator of efficacy. Therefore, there is a lack of information on the effectiveness of OA in reducing 24-h BP, daytime BP, nighttime BP, and morning BP as well as in restoring the circadian rhythm of BP.

According to recent studies, uncontrolled nocturnal BP is particularly common in hypertensive patients on antihypertensive medication, with an incidence rate of 30–60% depending on the study cohort. Mean nighttime BP is a better predictor of cardiovascular events than daytime BP or 24-h mean BP. A prospective cohort

study demonstrated that every 20mmHg increase in nighttime BP was associated with a 23% increase in the risk of all-cause mortality and a 36% increase in cardiovascular and cerebrovascular events. Controlling nighttime BP and restoring the circadian rhythm of BP are effective ways of reducing the risk of cardiovascular and cerebrovascular events in hypertensive patients.

However, managing nocturnal BP is challenging in practice. Antihypertensive chronotherapy may provide a new direction for effective management of nocturnal BP. A recently published multicenter, prospective, randomized controlled study from Spain (known as Hygia Chronotherapy Trial) found that taking antihypertensive medication before bedtime significantly reduced the risk of cardiovascular death, myocardial infarction, and major cardiovascular composite events (including coronary revascularization, heart failure, or stroke) in hypertensive patients. However, a two-center randomized, crossover, prospective clinical study performed in London and Thessaloniki suggested that the timing of antihypertensive drug delivery (morning vs. nighttime) did not affect 24-h BP, daytime BP, or nocturnal BP levels in hypertensive patients. Furthermore, the clinical evidence for antihypertensive chronotherapy comes mostly from populations on a single antihypertensive agent in Europe or the USA or from populations with cardiovascular disease. High heterogeneity, including in intervention methods, evaluation indicators, and study populations, between these studies has been noted. Moreover, a systematic review of 21 studies that compared antihypertensive medication taken in the morning with that taken at bedtime indicated that both dosing strategies showed no statistical

67 difference in 24-h mean BP reduction values. Thus, the clinical benefit of taking  
68 antihypertensive drugs before bedtime remains controversial.

69 Therefore, we planed to initiate this prospective, randomized, open-label,  
70 parallel-group clinical study to compare the effects of morning and bedtime  
71 administration on nocturnal BP reduction and recovery of circadian rhythm in patients  
72 with essential hypertension. The results of this trial are expected to provide useful  
73 guidance for optimizing BP control, particularly in Chinese patients with  
74 hypertension.

75 **Primary Objective:**

76 The decrease in average nocturnal SBP between baseline and after 12 weeks of the  
77 intervention.

78 **Secondary Objective:**

79 24-h ambulatory BP measurements

80 1. Reductions in 24-h, daytime and morning average SBP and diastolic BP (DBP) at  
81 weeks 4 and 12.

82 2. Average 24-h, daytime, nocturnal SBP and DBP control rates at weeks 4 and 12.

83 3. Changes of proportion of non-dipper, and changes in BP load.

84 Office BP measurements

85 (1) The reduction in average SBP and DBP in the clinic at weeks 4, 8, and 12.

86 (2) Office BP control rates.

87 (3) The treatment response rate (SBP <140 mmHg or a decrease $\geq$ 20 mmHg and DBP  
88 <90 mmHg or a decrease $\geq$ 10 mmHg) at weeks 4, 8, and 12.

Proportion of patients requiring intensive treatment.

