**Exclusion Criteria:**

1. Extreme dipper (nocturnal BP >20% lower than daytime BP).
2. Pregnancy, planning a pregnancy, or breastfeeding.
3. Renal artery stenosis.
4. Hyperkalemia (serum potassium >5.5 mmol/L), chronic renal insufficiency (creatinine >265µmol/L).
5. History of or progressing toward malignant hypertension, hypertensive emergency, hypertensive crisis, or hypertensive encephalopathy during the 2-week antihypertensive drug withdrawal phase and enrollment.
6. History of drug use or other causes of angioedema or a history of hypersensitivity to angiotensin receptor antagonists, angiotensin-converting enzyme inhibitors, or renin inhibitors.
7. History of alcohol or drug abuse.
8. Working at night or shift work.

9. Cardiovascular disease, such as unstable angina, heart failure, life-threatening arrhythmias, atrial fibrillation, renal failure, hypertrophic cardiomyopathy, and grade III–IV retinopathy.

10. Unable to tolerate ambulatory BP measurement or participate in clinical research.

11. History of allergy to amlodipine.

12. History of hemorrhagic stroke.

13. Participating in or planning to participate in other trials.

14. Poor compliance.

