**Collection of medical data and quality control:**

This research is initiated by [name] at the Hypertension Center, West China Hospital, Sichuan University. Trained physicians, nurses, and clinical research coordinators (CRCs) are required to keep medical records and collect data in accordance with the study protocol.

Baseline data on demographic characteristics, height, and body weight will be collected, and blood biochemistry tests will be performed. Office BP will be measured using calibrated electronic sphygmomanometers (HBP-9020, Omron Corp., Kyoto, Japan) according to the guidelines for the management of hypertension (However, due to budget constraints, we decided to switch to the Omron HBP-1100-E (Omron Healthcare Co., Ltd, Kyoto, Japan) before the trial commenced). To obtain accurate BP data, all participants are requested to rest for 5 min before the measurement. SBP and DBP are obtained three times on the right arm in a sitting position, with the average of the last two values calculated as mean office BP. ABPM

readings are obtained from the non-dominant arm at baseline and weeks 4 and 12 using a TM2430 BP monitor (A&D Inc., Tokyo, Japan). During monitoring, BP is measured at 20 min intervals throughout the day (usually from 6 am to 10 pm) and then at 30 min intervals at night (usually from 10 pm to 6 am). Valid recordings will span >20 h, including at least 20 during the day and 10 during the night. A diary card is issued to each participant so that they can record their schedule in detail, including the times they go to bed and wake up. The mean 24-h BP was calculated as the average of all successful values. Nighttime BP was defined as the mean BP recorded between falling asleep and waking up. Daytime BP was defined as the mean value of all other readings. Morning BP was defined as the average BP within 2 hours after waking up. Circadian rhythms were categorized according to the extent of nocturnal fall in BP: extreme dipper (>20% fall); dipper (10-20% fall); non-dipper (0 to <10% fall); and reverse dipper (<0% fall). The nocturnal fall in BP was calculated as (Daytime BP-Nighttime BP)/Daytime BP\*100%. BP load was defined as the percentage of readings above the normal value during the daytime, nighttime, or 24-h period.

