#### **Statistical Method:**

The study population is divided into a morning administration group and a bedtime administration group. Quantitative variables will be summarized as the mean  $\pm$  SD or as the median [interquartile range (IQR)] depending on the type of the original data.

Qualitative variables will be presented as the absolute and relative frequency. Quantitative variables will be compared between the two study groups using the t-test or Mann-Whitney U test and qualitative variables using the chi-squared test or Fisher's exact test.

All analyses will be based on the intention-to-treat (ITT) and the per-protocol (PP) populations. The primary objective of the study will be analyzed using an analysis of covariance (ANCOVA) model with appropriate baseline adjustments. The ANCOVA model will also be used to evaluate the other secondary objectives. Mean differences or odds ratios will be determined across groups along with their 95% confidence intervals. All statistical analyses will be performed using SPSS version 26.0 (IBM Corp., Armonk, NY, USA). The significance level will be set to 5% for all statistical tests.

The process for handling missing data is generally divided into the deletion of cases with missing data and imputation of missing data. The commonly used methods include mean imputation, last observation carried forward, and multiple imputation. We will deal with the missing data depending on the circumstances under the guidance of the Department of Clinical Research Management at West China Hospital.

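### Recovery of circadian rhythm is in the stated aim, but no objective estimates the between-arm difference in nocturnal fall (%), which the plan already calculates: a cheap improvement

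*Combined protocol and SAP*

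**What the plan says.** The Introduction closes with the aim of comparing morning and bedtime "administration on nocturnal BP reduction and recovery of circadian rhythm in patients" with essential hypertension. The primary objective and the sample size concern nocturnal SBP only. Rhythm appears in the ambulatory secondary objectives, item 3: "Changes of proportion of non-dipper, and changes in BP load". Items 1 and 2 of that list name weeks 4 and 12; item 3 names no visit.

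The section on collection of medical data and quality control defines the underlying measure: "The nocturnal fall in BP was calculated as (Daytime BP-Nighttime BP)/Daytime BP", expressed in per cent. It is used there to form four categories, among them "non-dipper (0 to <10% fall); and reverse dipper (<0% fall"). The same section says that ambulatory "readings are obtained from the non-dominant arm at baseline and weeks 4 and 12". BP load, the other half of item 3, is the share of readings above normal and does not describe the day-night pattern.

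Under Statistical Method: "The ANCOVA model will also be used to evaluate the other secondary objectives", with mean differences or odds ratios and 95% confidence intervals.

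**The concern.** Cutting a continuous measure discards information. With a cut at 10%, a patient whose fall goes from 1% to 9% counts as unchanged, and one who goes from 9.9% to 10.1% counts as recovered. The plan gives no reason for making the cut the only rhythm endpoint. Most of its other dichotomised BP endpoints, such as the control rates, stand beside a mean reduction in the same pressure. The nocturnal fall has no such companion.

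At stake is a secondary question: whether dosing time changes the day-night pattern. A real difference could be missed on the proportion although the same recordings would show it on the percentage scale.

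**Working it through.** **Inputs from Sample Size Consideration.** Difference 3 mmHg, SD 12 mmHg, two-sided 5%, power 85%, 289 evaluable per arm. The documents give no SD or mean for the nocturnal fall, no non-dipper rate, no on-treatment daytime SBP and no expected daytime difference. These are assumed below and varied.

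**Step 1: the plan's own figure.** n = 2 × (1.960 + 1.036)² × (12/3)² = 287.3, so 288 per arm by the normal formula. The t-test gives 288.3, so 289. The stated figure reproduces. Power at 289 is Φ(0.25 × √(289/2) − 1.960) = Φ(1.045) = 85%.

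**Step 2: the same standardised effect on a cut scale.** Suppose the fall is normal with equal SD in both arms and differs by 0.25 SD. If p₁ of the morning arm are non-dippers, then p₂ = Φ(z(p₁) − 0.25). With p̄ the mean of p₁ and p₂, power is Φ{(|p₁ − p₂| − 1.96 √[2p̄(1−p̄)/n]) / √[(p₁(1−p₁) + p₂(1−p₂))/n]}.

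| Non-dippers, morning arm | Bedtime arm | Power, proportion | Power, continuous |
|---|---|---|---|
| 50% | 40.1% | 67% | 85% |
| 60% | 50.1% | 67% | 85% |
| 70% | 60.8% | 64% | 85% |
| 80% | 72.3% | 58% | 85% |

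For 85% power the proportion would need about 455 per arm (50-60% non-dippers) to 548 (80%), against 288 for the continuous fall. Adjusting both analyses for baseline does not close the gap. In a simulation with an assumed baseline correlation of 0.3-0.5, ANCOVA had 87-93% power and baseline-adjusted logistic regression 59-73%, a loss of about 19-32 points.

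**Step 3: a scenario on the fall itself.** Assume a 3 mmHg nocturnal difference, no daytime difference and daytime SBP 135 mmHg. The difference in fall is 3/135 = 2.22 points. Worked case with SD 8 and morning-arm mean 8%:
- Fall below 10%: Φ((10 − 8)/8) = 59.9% against Φ((10 − 10.22)/8) = 48.9%.
- Power of the proportion: Φ((0.110 − 0.081)/0.041) = 76%.
- Power of the continuous fall: Φ(2.22/8 × 12.02 − 1.96) = 92%. The loss is 16 points.

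Across morning-arm mean falls of 5%, 8% and 10%:

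| SD of fall (points) | Continuous | Proportion with fall <10% | Loss (points) |
|---|---|---|---|
| 6 | 99% | 91-94% | 5-9 |
| 7 | 97% | 82-86% | 11-15 |
| 8 | 92% | 72-76% | 16-20 |
| 9 | 84% | 63-66% | 19-22 |

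At daytime SBP 125 mmHg the loss is 3-20 points over the same grid.

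**Step 4: vary the daytime difference.** Keep 135 mmHg by day in the morning arm, 3 mmHg lower at night in the bedtime arm, SD 6-9 and the same mean falls.
- Bedtime arm 1 mmHg lower by day: loss 17-26 points.
- 2 mmHg lower: the difference in fall is about 0.8-0.9 points and the loss 6-16 points.
- 3 mmHg lower: with mean fall 8%, the bedtime fall is (132 − 121.2)/132 = 8.18%, a difference of 0.18 points. Both analyses have about 3-7% power and the loss is about 1 point or less.
- 1.5 mmHg higher by day: both analyses have at least 92% power and the loss is 0-7 points.

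**Step 5: the literal category.** The figures in steps 3 and 4 take non-dipper as any fall below 10%. Read literally as 0 to <10%, with reverse dippers apart, a move from reverse dipper to non-dipper offsets a move from non-dipper to dipper. In the worked case of step 3 the proportions become 44.0% and 38.8%, and power drops from 76% to 24%. It was lower than for fall <10% in every scenario of step 3.

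All these figures assume normality and ignore the truncation from excluding extreme dippers at entry.

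**The case against.** The strongest reply is that the plan already analyses both components on their full scale: nocturnal SBP reduction is the primary endpoint and daytime SBP reduction is in secondary item 1. A reader can see whether night pressure fell more than day pressure. This stands in part. Two separate mean differences show the direction, but give no between-arm estimate or confidence interval for the fall.

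A second reply is that recovery naturally means moving into the dipper range. The plan defines an extreme-dipper category and excludes such patients at entry ("Extreme dipper (nocturnal BP >20% lower than daytime BP"). A larger mean fall can come from dippers becoming extreme dippers, so replacing the proportion would change the question as well as the power. This stands, and it is why the continuous fall should be added and the proportion kept.

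A third reply is that rhythm is one part of one secondary item with no power claim, and the trial's title names only nocturnal BP. This also stands. A reader might infer that half the trial's purpose is underpowered; the primary objective and sample size do not support that. Nor do the documents support the inference that a non-significant proportion would be reported as no recovery. They state no such rule and call for confidence intervals.

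**Conclusion.** The gap is real but modest. A quantity that bears directly on part of the stated aim is calculated and then analysed only after being cut. The primary result is untouched.

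It is tempting to attach one figure to the loss, such as 10-20 points of power. The documents do not support a single figure, because the SD and mean of the fall, the non-dipper rate and the daytime difference are all missing. With 289 per arm:
- At an assumed 0.25 SD, power is 85% against about 58-67% with 50-80% non-dippers.
- At 3 mmHg by night, none by day, daytime SBP 135 mmHg and SD 6-9, the loss is about 5-22 points for fall <10%.
- It is about 6-16 points if the bedtime arm is also 2 mmHg lower by day, and about 1 point or less if it is 3 mmHg lower.
- Under the literal 0 to <10% reading, the loss is larger in the scenario with no daytime difference.

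The continuous analysis had the higher power in every scenario computed. This is a cheap improvement, not a defect that threatens the trial's conclusion.

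**What to change.** In item 3 of the ambulatory secondary objectives, add the change in nocturnal SBP fall (%) from baseline to weeks 4 and 12. Analyse it with the ANCOVA already planned under Statistical Method, with baseline nocturnal fall as covariate, and report the between-arm mean difference with its 95% confidence interval.

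Keep the non-dipper proportion as a planned endpoint. Show all four dipper categories by arm and visit beside it, so that a larger mean fall is not read as recovery when it comes from extreme dipping.

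The change costs one line in the objectives and one further secondary analysis, on a scale less familiar to clinicians than a proportion. It needs no new recordings, visits or patients.

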### **Study Design:**

This prospective, multicenter, randomized, open-label, parallel-group clinical trial will be performed at 20 hospitals across Sichuan in China. However, in practice, 15 sites fulfilled the study protocol and conducted the study.

Study participants will be randomized in a 1:1 ratio to a morning (6–10 am) or a bedtime (6–10 pm) administration group. Initially, each participant will receive one tablet of OA (20/5 mg) daily for 4 weeks and will be then followed up at 4-week intervals for a total of 12 weeks. The OA dosage will be adjusted according to the results of ABPM and OBPM during follow-up. Controlled BP is defined as a 24-h mean BP <130/80 mmHg, daytime mean BP <135/85 mmHg, nighttime mean BP <120/70 mmHg, and OBPM <140/90 mmHg. The OA dosage will be increased to 1.5 tablets/day in patients who are found to have masked or sustained uncontrolled hypertension at the initial follow-up visit. If BP remains uncontrolled after a further 4 weeks, the OA dosage can be increased further to 2 tablets/day. All participants are instructed to discontinue their preexisting antihypertensive medications for at least 2 weeks before starting the trial intervention. Adherence with medication will be recorded at each follow-up visit. Concomitant use of other antihypertensive drugs other than OA will be prohibited during this study.

### **Study Duration:**

The study started in June 2022 and is scheduled to conclude in September 2023. However, due to the longer preparation of two sites, the follow-ups of patients were

lasted until April 2024.

**Inclusion Criteria:**

1. Patients with essential hypertension, aged 18–75 years, of either sex, with regularly scheduled activities and work and rest durations.
2. Patients who have not previously received antihypertensive treatment or stopped using antihypertensive agents for 2 weeks before starting the trial medication.
3. Able to provide a signed informed consent form and willingness to attend for follow-up in a timely manner.

**Exclusion Criteria:**

1. Extreme dipper (nocturnal BP >20% lower than daytime BP).
2. Pregnancy, planning a pregnancy, or breastfeeding.
3. Renal artery stenosis.
4. Hyperkalemia (serum potassium >5.5 mmol/L), chronic renal insufficiency (creatinine >265µmol/L).
5. History of or progressing toward malignant hypertension, hypertensive emergency, hypertensive crisis, or hypertensive encephalopathy during the 2-week antihypertensive drug withdrawal phase and enrollment.
6. History of drug use or other causes of angioedema or a history of hypersensitivity to angiotensin receptor antagonists, angiotensin-converting enzyme inhibitors, or renin inhibitors.
7. History of alcohol or drug abuse.
8. Working at night or shift work.

9. Cardiovascular disease, such as unstable angina, heart failure, life-threatening arrhythmias, atrial fibrillation, renal failure, hypertrophic cardiomyopathy, and grade III–IV retinopathy.

10. Unable to tolerate ambulatory BP measurement or participate in clinical research.

11. History of allergy to amlodipine.

12. History of hemorrhagic stroke.

13. Participating in or planning to participate in other trials.

14. Poor compliance.

**Collection of medical data and quality control:**

This research is initiated by [name] at the Hypertension Center, West China Hospital, Sichuan University. Trained physicians, nurses, and clinical research coordinators (CRCs) are required to keep medical records and collect data in accordance with the study protocol.

Baseline data on demographic characteristics, height, and body weight will be collected, and blood biochemistry tests will be performed. Office BP will be measured using calibrated electronic sphygmomanometers (HBP-9020, Omron Corp., Kyoto, Japan) according to the guidelines for the management of hypertension (However, due to budget constraints, we decided to switch to the Omron HBP-1100-E (Omron Healthcare Co., Ltd, Kyoto, Japan) before the trial commenced). To obtain accurate BP data, all participants are requested to rest for 5 min before the measurement. SBP and DBP are obtained three times on the right arm in a sitting position, with the average of the last two values calculated as mean office BP. ABPM

readings are obtained from the non-dominant arm at baseline and weeks 4 and 12 using a TM2430 BP monitor (A&D Inc., Tokyo, Japan). During monitoring, BP is measured at 20 min intervals throughout the day (usually from 6 am to 10 pm) and then at 30 min intervals at night (usually from 10 pm to 6 am). Valid recordings will span >20 h, including at least 20 during the day and 10 during the night. A diary card is issued to each participant so that they can record their schedule in detail, including the times they go to bed and wake up. The mean 24-h BP was calculated as the average of all successful values. Nighttime BP was defined as the mean BP recorded between falling asleep and waking up. Daytime BP was defined as the mean value of all other readings. Morning BP was defined as the average BP within 2 hours after waking up. Circadian rhythms were categorized according to the extent of nocturnal fall in BP: extreme dipper (>20% fall); dipper (10-20% fall); non-dipper (0 to <10% fall); and reverse dipper (<0% fall). The nocturnal fall in BP was calculated as (Daytime BP-Nighttime BP)/Daytime BP\*100%. BP load was defined as the percentage of readings above the normal value during the daytime, nighttime, or 24-h period.

The medical officer assigned to each study participant is alerted to remind the participant to attend all interventions and assessments in an effort to minimize the dropout rate. Participants and their caregivers also have direct access to a hotline during office hours if they have any concerns or problems. All original research data are entered into the electronic data capture system, namely, the Red Shine Chronic Disease Management System developed by the Hypertension Center at West China

Hospital (<http://47.108.235.3:3003/#/login>). All study-related information is stored securely in the system and all information concerning individual study participants is stored in locked filing cabinets in areas with limited access. A training session on the study protocol was provided before initiation of the study at each participating site to ensure that the quality of this clinical trial is satisfactory. On-site monitoring at the beginning, middle, and the end of the study is performed by assigned clinical researchers to ensure complete compliance with the study protocol. A project specialist has been assigned to this trial for data monitoring, examination, and cleaning. This specialist will perform the interim analyses, the frequency of which will be decided by the specialist in consultation with the principal investigator. The specialist will advise the principal investigator of the interim findings if necessary. After data cleaning is completed, the data managers and statisticians will conduct a final review of unresolved data issues, discuss the division of datasets together according to the statistical analysis plan, and examine any reports of serious adverse events. A statistical analysis is to be conducted halfway through and at the end of the trial. The subjects will be discontinued from follow-up if individual participants report any serious adverse effects during the intervention or a significant deterioration in their mental or physical state.

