#### **Sample Size Consideration:**

Considering the lack of published studies on the nocturnal systolic BP reduction after treatment with a fixed-dose OA combination, we referred to the study on BP control reported by Wang et al. , in which nocturnal systolic BP was reduced by  $-14.7 \pm$

11.6 mmHg in patients who received a fixed-dose combination of valsartan/amlodipine. We also collected and analyzed the medical data for 50 patients who had received OA at our center. Our preliminary analysis revealed that the standard deviation (SD) for nocturnal SBP reduction was 12 mmHg in subjects who took OA for 3 months. According to the above analysis, we set SD as 12 when calculating the sample size. In terms of the endpoint, a superiority margin of 3mmHg was considered a clinically meaningful BP reduction on the basis of the observed decreases in cardiovascular morbidity with small reductions in systolic BP (2-5mmHg) by pharmacological therapy. After discussion with clinical experts, we selected 3 mmHg as the superiority margin. Hence, while the significance level was set to 0.05 (two-sided) and the power to 85%, 289/289 cases would be needed for each category. Assuming a 20% dropout rate, each study group would comprise at least 360 patients, for a total of 720 cases. PASS version 15.0 was used to calculate the sample size.

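### Read with the plan's own categories, the non-dipper endpoint leaves out reverse dippers, so it can dilute, hide or reverse an effect on circadian rhythm

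*Combined protocol and SAP*

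**What the plan says.** The last paragraph of the Introduction gives two things to compare between morning and bedtime dosing: nocturnal BP reduction and "recovery of circadian rhythm in patients" with essential hypertension. Under Secondary Objective, the third ambulatory item carries the second of these: "Changes of proportion of non-dipper, and changes in BP load". It states no time point, no direction of benefit and no grouping of categories.

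The term is defined in one place, the section on collection of medical data and quality control. After the extreme-dipper class (a fall above 20%), the remaining classes are "dipper (10-20% fall); non-dipper (0 to <10% fall); and reverse dipper (<0% fall". They do not overlap. The fall itself is given by "The nocturnal fall in BP was calculated as (Daytime BP-Nighttime BP)/Daytime BP", times 100%, without saying whether systolic or diastolic pressure is used.

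The Exclusion Criteria bar one dipping pattern, "Extreme dipper (nocturnal BP >20% lower than daytime BP". Reverse dippers can therefore enter. The Statistical Method section has no rule specific to dipping; it says only "The ANCOVA model will also be used to evaluate the other secondary objectives", and that mean differences or odds ratios will be given with 95% confidence intervals.

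**The concern.** A proportion in a middle band is not monotone in the quantity being banded. A patient can leave the 0 to <10% band upwards, by dipping more, or downwards, by becoming a reverse dipper; the count falls by one either way. A patient who moves up from reverse dipping into the band adds one. If fewer non-dippers is read as recovery, which is the natural reading of the aim, some improvement counts against the better arm and some deterioration counts for the worse one.

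This is the only planned endpoint that classifies the day-night pattern. At stake is whether the trial's answer on circadian rhythm has the right size and the right sign.

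**Working it through.** **What the documents allow to be reproduced.** They give no figure for the circadian endpoint. The primary sample size reproduces: 2 × (1.960 + 1.036)² × 12² / 3² = 287.3, so 288 per group by the normal approximation and 289 by the t distribution, as stated. It matters here only as an arm size.

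**Step 1: score each move.** Change in the count when one patient moves, using the plan's bands:

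| Move | Middle band (0 to <10%) | Any fall <10% |
|---|---|---|
| Reverse to non-dipper | +1 | 0 |
| Non-dipper to reverse | −1 | 0 |
| Reverse to dipper | 0 | −1 |
| Dipper to reverse | 0 | +1 |
| Non-dipper to dipper | −1 | −1 |
| Dipper to non-dipper | +1 | +1 |
| Non-dipper to extreme dipper | −1 | −1 |

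The middle band scores moves across the 0% boundary backwards and misses moves between reverse dipper and dipper. With any fall <10%, no deeper fall raises the count and no shallower fall lowers it. This step needs no assumption.

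**Step 2: effect of a shift in the mean fall.** All inputs are assumed: nocturnal fall normal with SD 7 points; one arm's mean deeper by 2.2 points (3 mmHg on a daytime SBP of 135, 3/135 = 2.2%, daytime pressure unchanged). For mean m:

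- middle band = Φ((10 − m)/7) − Φ((0 − m)/7)
- fall <10% = Φ((10 − m)/7)

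Example, m = 2: 0.8735 − 0.3875 = 0.486. Shifted to 4.2: 0.7963 − 0.2743 = 0.522.

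| Comparator mean fall | Reverse dippers implied | Middle band | Fall <10% | Middle band shows |
|---|---|---|---|---|
| 2% | 39% | 48.6% to 52.2% (+3.6) | 87.3% to 79.6% (−7.7) | wrong sign |
| 4% | 28% | 52.0% to 51.9% (−0.1) | 80.4% to 70.6% (−9.8) | effect hidden |
| 6% | 20% | 52.0% to 48.1% (−3.9) | 71.6% to 60.1% (−11.5) | effect diluted |
| 8% | 13% | 48.6% to 41.6% (−7.0) | 61.2% to 48.9% (−12.3) | effect diluted |

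**Step 3: where the sign turns.** The band is symmetric about 5, so its probability depends only on the distance of the mean from 5. Means m and m + 2.2 give the same value when m + 1.1 = 5, that is m = 3.9, whatever the SD. Below 3.9 the middle band rises when dipping improves; above it, the band falls. Putting SD 6, 8 or 9 into the same formula at m = 2 gives 53.9% to 59.1%, 44.0% to 46.6% and 40.1% to 42.0%: the same wrong sign.

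**Step 4: could it reach significance?** Assume 45% non-dippers and 20% reverse dippers, 289 patients per arm, and half the reverse dippers in one arm becoming non-dippers while the other arm does not change. The proportions are 55% (159/289) and 45% (130/289). The odds ratio is (159 × 159)/(130 × 130) = 1.50, with p = 0.016 by uncorrected chi-squared: more non-dippers in the arm that improved. The <10% proportion is 65% in both arms, so it misses this improvement but does not reverse it.

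**The case against.** The best reply is that the endpoint item may use non-dipper loosely for any fall below 10%, and that the plan defines all four classes and presents qualitative variables as frequencies, so movement into the reverse or extreme class would be visible. That is possible, and no text confines reporting to one band. But no text pools reverse dippers with non-dippers either, and the only definition given separates them. Leaving the choice open in an open-label trial also allows it to be made after the data are seen.

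Second, the wrong sign needs a low mean fall, with 28% or more reverse dippers in the first two rows of the table. This stands. At higher means the endpoint moves the right way, and the remaining fault is dilution.

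Third, nocturnal SBP reduction (primary) and daytime reduction (secondary) are analysed directly, so a trial-level change in the day-night difference would not be wholly lost. This limits the consequence but does not repair the one endpoint that classifies the pattern.

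A reader might infer more than the documents support. Not every improvement from reverse dipping counts against an arm: full recovery to dipper scores zero. Success and failure are not the plan's terms, since it states no responder rule and no direction of benefit. Nor is crediting extreme dipping peculiar to the middle band: a move from non-dipper to extreme dipper lowers the <10% proportion too. In the 8% row, extreme dipping rises from 4.3% to 8.1% under either definition.

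**Conclusion.** The point holds as a fault in how a secondary endpoint is defined. It follows from the plan's own categories and from an exclusion list that lets reverse dippers in. Following the text as written gives a measure that is not monotone in nocturnal fall.

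The size is illustrative only. Under a normal fall, SD 7 and a 2.2-point shift, the result runs from a 3.6-point movement in the wrong direction (mean 2%), through no visible effect (mean 4%), to a correct sign with 3.9 points shown instead of 11.5 (mean 6%) or 7.0 instead of 12.3 (mean 8%). Which case applies depends on the mean fall in the enrolled patients, which the documents do not give. They do not support a claim that the sign will be wrong in this trial. The primary endpoint, its analysis and the sample size are untouched.

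**What to change.** Define the endpoint as the proportion of patients with a nocturnal SBP fall below 10% (non-dipper plus reverse dipper) at weeks 4 and 12. Compare arms by logistic regression adjusted for baseline percentage fall, and state that a lower proportion is the favourable direction. Add the continuous percentage fall by ANCOVA as a supporting analysis; it also picks up moves from reverse dipper to non-dipper, which the <10% proportion cannot see. Because moves to extreme dipping lower the <10% proportion, report the frequency of a fall above 20% separately by arm.

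The cost is wording. Everything needed comes from the ambulatory recordings already scheduled at baseline and weeks 4 and 12. If the change is made after outcome data have been seen, say so and show the middle-band result beside the new one.
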